### Sample size

2.5

The sample size will be calculated based on the primary outcome (24h UP). According to a previous study,^[34]^ the average 24h UP level of the control group is 100.6 mg/24 h, with a standard deviation of 23 mg/24 h. After LDP treatment, the average 24 h UP level in the experimental group was 89 mg/24 h, with a standard deviation of 12 mg/24 h. The following formula is employed to calculate the sample size that allows obtaining a significantly lower 24h UP in the experimental group after 24 weeks of treatment: 

where *σ*^2^ is the overall variance, estimated as the sample variance *s*^2^: 

The proportion of participants between the experimental and control groups is set to 1:1 (*k* = 1). The study is designed to have a power of approximately 90% and a 2-sided significance level of 0.05 (*a* = 0.05, *β* = 0.1). *μ*_2_, *μ*_1_, *s*_1_, and *s*_2_ are the mean and standard deviations in the control and experimental groups, respectively. This resulted in *n* = (1.96 + 1.28)^2^ × (23^2^ + 12^2^)/(100.6–89)^2^ ≈ 56. Thus, after assuming a dropout rate of 10%, the sample size for patients with DKD in each group was determined as 62, and the total sample size is 124.

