### Outcome measures

3.2

Primary outcome: The primary outcome is determined as the change in 24h UP, from the baseline to the end of the treatment phase (week 24).

Secondary outcomes:

1.Changes in SCr and eGFR: eGFR will be used to assess the kidney function of participants with CKD-EPI creatinine equation of 2009^[37]^ (at weeks 4, 8, 12, 16, 20, 24).2.Change in the urinary albumin excretion rate from baseline to week 24 (at weeks 4, 8, 12, 16, 20, 24).3.Improvement of TCM syndromes and symptoms from baseline to week 24 (at weeks 4, 8, 12, 16, 20, 24).4.Changes in FBG and postprandial 2-hour blood glucose (2h PG) from baseline to week 24 (at weeks 4, 8, 12, 16, 20, 24).5.Changes in blood lipids from baseline to week 12 and week 24, including total cholesterol, triglyceride, HDL cholesterol, and LDL cholesterol (at weeks 4, 8, 12, 16, 20, 24).

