### Statistical analysis

3.7

All data analyses will be conducted according to the intention-to-treat principle. Missing values will be replaced by the last observation carried forward method. Two similar participants with complete data will be double-checked to ensure that the data are correct before analysis.

The data will be analyzed using the Statistical Package for the Social Sciences version 22.0 (SPSS 22.0, Chicago, IL). The analytical methods will be selected according to the distribution characteristics of the data. The measurement data will be examined using group *t* tests or nonparametric tests, the count data will be tested using the Chi-square test or Fisher exact probability method, and the grade data will be evaluated using nonparametric tests. Compared with the baseline values, the measurement data will be assessed using paired *t* tests or nonparametric tests, and the count data will be examined using a nonparametric test. All statistical tests will be bilateral tests, and *P* values <.05 will indicate statistical significance.

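### The primary change in 24h UP is compared without baseline adjustment, by a t test or rank test chosen from the observed data under no stated rule; this is valid but inefficient and leaves the estimated quantity open

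*Protocol article*

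**What the plan says.** Section 3.2 (Outcome measures) defines the endpoint: "The primary outcome is determined as the change in 24h UP, from the baseline to the end of the treatment phase (week 24").

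Section 3.7 (Statistical analysis) names no test for that endpoint. It gives a general rule, "The analytical methods will be selected according to the distribution characteristics of the data", and for continuous outcomes the between-group options "The measurement data will be examined using group *t* tests or nonparametric tests". Baseline enters only through a within-group comparison: "Compared with the baseline values, the measurement data will be assessed using paired *t* tests or nonparametric tests". No normality criterion, default test, covariate or transformation is stated.

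Section 2.5 (Sample size) plans for "a power of approximately 90% and a 2-sided significance level of 0.05". Its inputs are levels of 24h UP, not changes: "the average 24h UP level of the control group is 100.6 mg/24 h, with a standard deviation of 23 mg/24 h" and "the average 24 h UP level in the experimental group was 89 mg/24 h, with a standard deviation of 12 mg/24 h".

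**The concern.** Two things are fixed badly.

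First, baseline 24h UP is measured in every participant, yet the treatment comparison uses it only by subtraction. A change score gives baseline a coefficient of exactly 1. The best linear coefficient is the regression slope of week 24 on baseline, which is the correlation times the ratio of the week-24 SD to the baseline SD. When that slope is below 1, subtracting the whole baseline adds noise that ANCOVA would remove. The paired tests do not help, because they compare each group with itself and not one treatment with the other.

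Second, the t test concerns a difference in means, and a rank test does not. If the choice waits for the observed distribution and no rule is written down, the quantity that the primary result estimates is unknown until the data are seen.

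At stake is precision in a trial whose Discussion lists small sample size as a limitation, and a primary result whose meaning is not settled in advance. The stated power was also worked out for levels, so it carries over to the change score only if the correlation is high enough.

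**Working it through.** **Inputs from section 2.5.** Control mean 100.6, SD 23; experimental mean 89, SD 12 (mg/24 h); two-sided alpha 0.05; target power 90%; 56 per arm before dropout. Hence difference = 100.6 − 89 = 11.6 and pooled SD = √((23² + 12²)/2) = √(673/2) = 18.34.

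**The plan's own figure.** (1.96 + 1.28)² × 673 / 11.6² = 10.4976 × 673 / 134.56 = 52.5, so 53 per arm and not the stated 56. The gap is on the safe side and is a separate matter. I keep 56 per arm, which gives 91.3% power by noncentral t for a comparison of week-24 levels.

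**Assumptions.** The article gives no correlation (rho) between baseline and week-24 24h UP, so I show 0.3, 0.5 and 0.7. The first table takes SD 18.34 at both times in both arms.

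**Formulas.**
- Change score: SD = 18.34 × √(2(1 − rho))
- ANCOVA: residual SD = 18.34 × √(1 − rho²)
- Standard error of the difference = SD × √(2/56)
- Variance ratio, ANCOVA to change score = (1 − rho²)/(2(1 − rho)) = (1 + rho)/2, which is below 1 for every rho below 1

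| rho | SD change | SD ANCOVA | Variance ratio | Power change | Power ANCOVA |
|---|---|---|---|---|---|
| 0.3 | 21.70 | 17.50 | 0.65 | 80.0% | 93.5% |
| 0.5 | 18.34 | 15.89 | 0.75 | 91.3% | 96.9% |
| 0.7 | 14.21 | 13.10 | 0.85 | 99.0% | 99.6% |

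The change-score test passes 90% at rho of about 0.48.

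**Unequal SDs.** The equal-SD assumption sits poorly with the plan's 23 and 12. Keep those as the week-24 SDs and assume a baseline SD of 23 in both arms (not in the article).
- Variance of change: control 2 × 529 × (1 − rho); experimental 529 + 144 − 2 × rho × 23 × 12. At rho 0.3 these are 740.6 and 507.4, so the standard error is √(1248.0/56) = 4.72.
- ANCOVA with a common slope b = rho × (529 + 276)/1058. At rho 0.3, b = 0.228, the residual variances are 484.1 and 133.8, and the standard error is √(617.9/56) = 3.32.
- Power, change score versus ANCOVA, both allowing unequal variances: about 68% versus 93% at rho 0.3, 81% versus 96% at 0.5, and 94% versus 99% at 0.7.

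**Type I error of a data-chosen test.** In simulation (20,000 runs, 56 per arm, three distributions), a fixed Shapiro-Wilk check followed by a t or rank test rejected a true null in 0.049 to 0.051 of runs. Running both tests and keeping the smaller p value gave 0.058 to 0.071.

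**The case against.** Much can be said for the plan.

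- **Validity.** A reader might infer that chance baseline imbalance biases the change score. It does not: under 1:1 randomisation the comparison is unbiased on average, and its standard error already reflects chance imbalance. Only the result conditional on an observed imbalance is shifted. This objection stands, and the point is one of efficiency.
- **Type I error.** A reader might infer that a data-chosen test is not protected at 5%. The article ties the choice to the distribution, not to the result, and a fixed check of that kind holds about 5%. Only choosing by result inflates the error, and the article does not propose that. What remains is that no rule is written that would exclude it.
- **Power.** The loss depends on an undocumented correlation. With equal SDs it is 0.6 points at rho 0.7, and the 90% target is met from about 0.48 upward. This stands too; the documents do not show that the trial is underpowered.
- **Log scale.** Unequal SDs might suggest that a log analysis is required. They do not show skew, and logging would not equalise them. The coefficients of variation are 23/100.6 = 22.9% and 12/89 = 13.5%, which correspond to log-scale SDs of about 0.226 and 0.134 if the data are log-normal.
- **An unseen SAP.** Section 3.7 is a general paragraph in an article, and detail may sit in a SAP. That would excuse silence. Here the article states the between-group tests and how they are chosen, so a SAP naming one adjusted model would depart from that text.

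**Conclusion.** The point holds as one of efficiency and of an unfixed estimand, and it should be fixed. The named analysis is valid but makes poorer use of baseline than ANCOVA, and it leaves open whether the primary result concerns means or ranks. With equal SDs the power gain from ANCOVA is about 13 points at rho 0.3, 6 at 0.5 and under 1 at 0.7. It is larger if the plan's unequal week-24 SDs are kept and baseline SD is 23. These sizes rest on an assumed correlation and assumed baseline SDs. The direction does not depend on which correlation below 1 is assumed in the equal-SD case. The documents do not support the stronger readings that the primary comparison is biased, that its 5% level is lost, or that a log transformation is needed.

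**What to change.** State one primary analysis in section 3.7, whatever the observed distribution: ANCOVA of week-24 24h UP on treatment with baseline 24h UP as covariate, using standard errors robust to unequal variance. Report the adjusted mean difference in mg/24 h with its 95% confidence interval. With baseline in the model, analysing week-24 value or change gives the same treatment estimate, so the outcome definition in section 3.2 can stay. A log transformation is optional; if wanted, it must be fixed before unblinding. Keep a rank-based test as sensitivity analysis only. Use the same baseline-adjusted form for the other continuous outcomes. If a SAP already does this, bring the two texts into line.

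The cost is one paragraph of wording, agreed before unblinding. Baseline is already collected and no participants are added. ANCOVA runs in the named SPSS 22.0; the analyst should confirm which procedure there supplies the robust standard errors.

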### Design

2.2

The proposed study is a prospective, double-blind, randomized, placebo-controlled clinical trial to evaluate the efficacy and safety of LDP compared with a placebo. The clinical trial number is ChiCTR2000029800, which has been registered in the Chinese Clinical Trial Registry (http://www.chictr.org.cn/showproj.aspx?proj=10862) on February 14, 2020. A 2-week run-in period will be initiated after obtaining the written informed consent. Next, 124 eligible participants will be randomly allocated to either the LDP group or the control group in a 1:1 ratio. After allocation, patients in the experimental group will receive basic treatment and LDP, while patients in the control group will be treated with the basic treatments and placebo. Both groups will undergo a 24-week treatment, with follow-ups at 0, 4, 8, 12, 16, 20, and 24 weeks. In this study, we aim to observe the efficacy and safety of LDP when compared with western medicine alone for DKD treatment. The Standard Protocol Items: Recommendations for Interventional Trials (SPIRIT) 2013 statement will be followed by this trial protocol (see Supplemental Digital Content: Additional file 1 and Fig. 1 for the schedule of enrollment, interventions, and assessments).^[33]^ The study flow chart is shown in Figure 2.

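### Before-after tests and secondary tests get the same unadjusted .05 significance status as the randomised comparison, although a before-after change in the LDP arm cannot be attributed to LDP

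*Protocol article*

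**What the plan says.** In the protocol article, the Statistical analysis section plans two kinds of test for continuous outcomes. The first is between groups: "The measurement data will be examined using group" t tests or nonparametric tests. The second is against baseline: "Compared with the baseline values, the measurement data will be assessed using paired" t tests or nonparametric tests. One closing rule covers both: "All statistical tests will be bilateral tests, and" P "values <.05 will indicate statistical significance". It makes no exception, ranks neither kind of test above the other and adjusts nothing.

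The Outcome measures section names one primary outcome at one time point: "The primary outcome is determined as the change in 24h UP, from the baseline to the end of the treatment phase (week 24". It then lists five secondary items that contain ten variables: SCr, eGFR, urinary albumin excretion rate, TCM syndrome, fasting glucose, 2-hour glucose and four lipids. Each item carries the same six post-baseline weeks in brackets, for example "Change in the urinary albumin excretion rate from baseline to week 24 (at weeks 4, 8, 12, 16, 20, 24". The lipid item gives two endpoint weeks ahead of its bracket: "Changes in blood lipids from baseline to week 12 and week 24, including total cholesterol".

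On background therapy, the Design section says "After allocation, patients in the experimental group will receive basic treatment and LDP", and the control arm receives the same basic treatment with placebo. The Treatment plan section gives that treatment as metformin and irbesartan, with diet and exercise advice.

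**The concern.** A paired test in one arm measures everything that changed since baseline: the study drug, the background drugs, diet, regression to the mean and time. The Introduction describes standard DKD treatment as acting on blood sugar, blood pressure, lipids and urine protein, which overlaps with the primary outcome and several secondary ones. Only the randomised contrast removes these shared influences. If both kinds of test carry the same significance label, a significant change under LDP beside a non-significant one under placebo is easily read as a treatment effect, which it is not.

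The .05 rule also covers many secondary comparisons, so one or more nominally significant results can be expected by chance. The Discussion hopes the findings will support use of the treatment for symptoms, which are a secondary outcome, so these results may carry claims.

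**Working it through.** **Inputs.** From the article: two-sided .05, which agrees between the Sample size and Statistical analysis sections; 56 evaluable patients per arm, 62 randomised; ten secondary variables; six post-baseline visits. The 56 is used as given. The printed formula yields (1.96 + 1.28)² × (23² + 12²) / (100.6 − 89)² = 10.4976 × 673 / 134.56 = 52.5, a separate matter that does not bear on this point. The article gives no size for the background change, so a range is assumed.

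**1. Before-after tests when LDP does nothing.** Let both arms change by the same d, in SDs of the change. The paired t test has n − 1 = 55 degrees of freedom and noncentrality d√56; call its power p. The arms are independent, so the chance that the LDP arm is significant and the placebo arm is not is p(1 − p).

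| d (assumed) | p | p(1 − p) |
|---|---|---|
| 0.1 | 0.114 | 0.101 |
| 0.2 | 0.313 | 0.215 |
| 0.25 | 0.452 | 0.248 |
| 0.3 | 0.597 | 0.241 |
| 0.4 | 0.837 | 0.137 |
| 0.5 | 0.957 | 0.041 |

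p(1 − p) cannot exceed 0.25, so the row at 0.25 SD is close to the worst case. With all 62 per arm, the values at 0.2, 0.25 and 0.3 SD are 0.225, 0.250 and 0.230. A two-sided .05 between-group test favours LDP by chance with probability 0.025.

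**2. How many secondary between-group tests.** The article can be read in three ways.

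- Week 24 only: 10 variables, 10 tests.
- Endpoints as defined: albumin excretion, TCM syndrome, fasting and 2-hour glucose at week 24 (4 tests); four lipids at weeks 12 and 24 (8); SCr and eGFR, which have no endpoint beyond the bracketed list, at one to six visits (2 to 12). Total: 4 + 8 + 2 = 14 to 4 + 8 + 12 = 24.
- Every listed visit: 10 × 6 = 60 tests.

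**3. Chance of at least one false positive.** For k independent tests with no true effects it is 1 − 0.95^k, and 0.05k false positives are expected.

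| k | expected | at least one, independent |
|---|---|---|
| 10 | 0.5 | 40% |
| 14 | 0.7 | 51% |
| 24 | 1.2 | 71% |
| 60 | 3.0 | 95% |

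These tests are not independent: eGFR is computed from creatinine, and each variable is measured repeatedly in the same patients. Correlated normal test statistics were therefore simulated (40,000 draws per setting). For 10 tests, a correlation of 0.5 between variables gives 28%. For 60 tests, the result runs from 93% (0.3 between visits, 0 between variables) to 52% (0.9 and 0.5). All these correlations are assumptions.

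**4. The primary outcome.** One variable, one time point and one between-group test at .05 give a type I error of .05, however many secondary tests follow.

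**The case against.** The strongest reply is that the trial is plainly built on the comparison with placebo. The Design section says so, the sample size rests on a between-group difference, and the group tests come first in the analysis section. A reader might infer that before-after changes will be reported as LDP effects. No sentence says that. The rule labels individual P values and does not turn a significant LDP arm beside a non-significant placebo arm into a treatment difference. Even the wording that these tests are run within each arm is the natural reading, not a statement. This stands: the problem is a label that invites misreading, not a declared false inference.

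A reader might also infer that every secondary outcome will be tested at every visit, making some positive finding nearly certain. That is not written either. The bracketed weeks may be the measurement schedule, and the schedule figure is not shown. Sixty tests is an upper bound, and even there the chance falls to 52% under strong correlation.

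The size of the background change is unknown. The two-week run-in and the entry limits on blood pressure and HbA1c suggest that many patients are already treated, which could make it small. The pattern then occurs in about 10% of trials at 0.1 SD, not 25%.

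Finally, secondary multiplicity is commonly left to an SAP. Silence on it would be no finding. Here, however, the article is not silent: it fixes one significance rule for all tests, and an SAP that made the before-after tests descriptive would depart from that text.

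**Conclusion.** The point holds in a limited form. The analysis section gives tests against baseline, and all secondary tests, the same unadjusted .05 status as the randomised comparison, and a before-after test in the LDP arm cannot isolate LDP from treatment that both arms receive. With no LDP effect, the misleading pattern occurs in about 4% to 25% of trials across assumed shared changes of 0.1 to 0.5 SD, peaking near 0.25 SD, against 2.5% for the proper test. For the secondary outcomes, the chance of at least one false positive under independence is 40%, 51% to 71%, or 95%, depending on how the visit lists are read. Under the assumed correlations it is 28% for 10 tests and 52% to 93% for 60.

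The primary conclusion is untouched. What is at risk is the reading of within-arm and secondary results. The lipid time points need only clarification.

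**What to change.** Amend the Statistical analysis section as follows.

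- Efficacy conclusions rest only on between-group comparisons, with week 24 as the contrast.
- Within-arm changes are shown as means with 95% confidence intervals and no P values.
- Each secondary measurement is analysed with a baseline-adjusted between-group model (ANCOVA, or a mixed model over visits), and intermediate visits are descriptive. The baseline values are already collected, and adjusting for them gains precision.
- Secondary results are labelled exploratory. A formal adjustment such as Holm is an alternative, but it costs power and is a matter of choice.

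In Outcome measures, give the lipid item one set of endpoint weeks and say whether the bracketed weeks are measurement times or analysis times.

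The cost is wording and a slightly different model, with no added patients, visits or assays. The downside is that fewer results can be called significant.

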## Discussion

4

As a valuable medical treatment, TCM is currently benefiting several individuals. The essence of TCM lies in treatment based on the differentiation of disease syndromes. Currently, TCM doctors regard TCM as a basic or complementary therapy in patients with endocrine diseases. LDP is usually prescribed for patients with DKD and could relieve the symptoms of DKD. This trial aims to examine the efficacy and safety of DKD compared with a placebo in the treatment of DKD. The quality of randomized controlled trials concerning Chinese medicine presents several challenges, including faulty study design and methodology and lack of trained investigators. To ensure the quality of this study and achieve a reliable conclusion, the experimental design and study performance will be performed under strict quality control. The findings of this trial could enable alternative treatment in patients with DKD; additionally, the findings may provide scientific evidence for the use in DKD to improve patients’ symptoms and control 24h UP levels. However, the small sample size in this study is a limitation. Nevertheless, the results will provide novel evidence regarding the effectiveness of adjuvant TCM in patients with DKD.
